#### **9.1.2.2 Sampling Method**

Participants will be recruited through convenience sampling. Convenience sampling is a common sampling method whose core features are convenience and economy (Sedgwick 2013). When conducting convenience sampling, the researcher selects those samples that are easily accessible, rather than obtaining samples through random selection. This means that the sample is usually chosen based on the convenience of the researcher, such as choosing volunteers or those who are easily accessible (Stratton 2021). It can help the researcher to obtain data quickly, but potential biases and limitations must be carefully considered when analysing and interpreting the results (Etikan et al. 2016).

#### **9.1.2.3 Sample Size Calculation**

Sample size was calculated using G\*Power 3.1. Assuming that the data is normally distributed, this study will use mixed model ANOVA to compare differences between

the effects of DD-10, S-10, and S-0 pressure garment on sensorimotor functions and quality of life among stroke patients at three different time points during the 8 weeks of application. With small to medium effect size,  $f$  of 0.125, power of 0.8,  $\alpha$  error of 0.05, three groups, and three measurements, the total sample size needed will be 132, as shown in Figure 4. With 44 people in each group and taking into account the 20 % dropout rate, by using the formula:  $N = n/(1-d)$ , i.e.,  $44/(1-0.2) = 55$ , there will be a total of 55 people in each group. Thus, the final sample size will be 165 patients ( $n$ : DD-10 Group = 55; S-10 Group = 55; S-0 Group = 55).

[figure not shown]

Figure 4. Sample Size Calculation

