### **9.1.6 Data Analysis**

Data will be analysed using SPSS 26.0 using Intention-to-treat (ITT) analysis. ITT analysis, which aims to minimize bias and maintain random allocation of study participants (Gupta 2011), is suitable to be used when there are shedding participants. Its key idea is to analyse the group to which the participant belongs in that initial allocation, regardless of whether they completed the study or received the intended intervention. In clinical trials, participants may drop out, refuse intervention, or deviate from the study protocol. The ITT analysis includes all participants regardless of whether they completed the study or followed the treatment plan. This helps prevent shedding bias, which may occur if only completers are analysed (Mccoy 2017). The study will use a imputation method, such as, Last Observation Carried Forward (LOCF) (Shao & Zhong 2003) or mean imputation (Jadhav et al. 2019), or multiple imputation (Austin et al. 2021), this will probably depend on the requirements of the data.

Both descriptive and inferential statistics will be used. Frequencies, means, and medians will be used to describe the demographic data (Fisher & Marshall 2009). A mixed model ANOVA to compare the outcome measures.

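### The 132 powers a group-by-time interaction, on which f = 0.125 means a week-8 gap of about 0.56 to 0.75 SD, not a small-to-medium effect; the planned ANOVA also does not adjust for baseline

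*Protocol*

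**What the plan says.** Protocol section 9.1.2.3 says that "this study will use mixed model ANOVA to compare differences between" the three garments at three time points. The planning values are introduced by "With small to medium effect size", then an f "of 0.125, power of 0.8" and an alpha of 0.05, with the result "three groups, and three measurements, the total sample size needed will be 132", or 44 per arm. After "taking into account the 20 % dropout rate", "there will be a total of 55 people in each group".

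The text does not say whether the powered effect is the between-arm main effect, the time effect or the group-by-time interaction. It gives no correlation between visits, no SD and no target difference in FMA points. Section 9.1.4.3 names the upper-extremity FMA as the primary outcome. On the analysis, section 9.1.6 says only: "A mixed model ANOVA to compare the outcome measures".

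**The concern.** A reader takes small to medium as a statement about how far apart the garments must be for the trial to detect it. In an interaction test, f is an average over nine group-by-visit cells. Three of these are baseline cells, where randomised arms do not differ in expectation. A modest f can therefore stand for a sizeable difference at the end of wear. Without an SD or an FMA-point target, the reader cannot see this.

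The analysis raises a second matter. A three-visit mixed ANOVA carries baseline as one of the outcomes, although it could be used as a covariate to remove between-patient variation. At stake are a realistic statement of what 132 completers can show, and some power that the collected data could supply.

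**Working it through.** **Inputs.** From section 9.1.2.3: f = 0.125, alpha 0.05, k = 3 arms, m = 3 visits, N = 132 (44 per arm), dropout 20%. From sections 4.0 and 5.0: visits at baseline, week 4 and week 8. Inferred: correlation ρ = 0.5 and sphericity, since the text gives neither and Figure 4 is not shown. SD means the within-arm SD at one visit.

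**1. The plan's figure.** For the interaction, λ = f²·N·m/(1−ρ) = 0.015625 × 132 × 3 / 0.5 = 12.4, with df (k−1)(m−1) = 4 and (N−k)(m−1) = 258. Power is 0.808; with 129 patients it is 0.797. So 132 is reproduced. The alternatives tried do not give it: within-factor test 105; between-factor test 417; two other effect-size conventions 387 and 390; interaction with ρ = 0.4, 156, and with ρ = 0.6, 105. The dropout step is correct: 44/0.8 = 55, and 3 × 55 = 165.

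**2. From f to a difference between arms.** Let δ be the largest week-8 difference in SD units, with no difference at baseline. If an arm profile g is scaled by a time course t, then f = δ × SD(g) × SD(t), each SD with divisor 3. The SD of (0, ½, 1) is √(1/6) = 0.408. The SD of (0, 1, 1), (0, 0, 1) or (1, 0, 0) is √(2/9) = 0.471.

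| Arms | Time course | f per unit δ | δ at f = 0.125 |
|---|---|---|---|
| S-10 halfway | steady build-up | 0.1667 | 0.75 SD |
| One or both compression arms effective | steady build-up | 0.1925 | 0.65 SD |
| S-10 halfway | full by week 4, or week 8 only | 0.1925 | 0.65 SD |
| One or both compression arms effective | full by week 4, or week 8 only | 0.2222 | 0.56 SD |

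Irregular monotone patterns go lower. If one compression arm is fully effective by week 4 and the other reaches the same level only at week 8, six of the nine interaction effects are ±δ/3. Then f = δ√(6/81) = 0.272δ, and δ = 0.46 SD. None of these conversions depends on ρ.

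**3. Baseline adjustment, both visits kept.** Given baseline, week-4 and week-8 values have variance 1−ρ² = 0.75 and covariance ρ−ρ² = 0.25. The inverse matrix has diagonal 1.5 and off-diagonal −0.5. With both compression arms effective, the squared deviations of the arm profile sum to 2/3. So λ = 44 × (2/3) × (1.5a² + 1.5b² − ab), where a and b are the week-4 and week-8 differences, with df 4 and 2(132−4) = 256. For the planned test, λ = (f per unit δ × 0.5)² × 132 × 3 / 0.5. At δ = 0.5:

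| Time course | Planned interaction | Joint baseline-adjusted test |
|---|---|---|
| Steady (a = 0.25, b = 0.5) | λ 7.33, 55% | λ 10.08, 71% |
| Full by week 4 (0.5, 0.5) | λ 9.78, 70% | λ 14.67, 88% |
| Week 8 only (0, 0.5) | λ 9.78, 70% | λ 11.00, 75% |

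With S-10 halfway the 2/3 becomes 1/2. Under steady build-up, λ = 44 × 0.5 × 0.344 = 7.56, and power goes from 43% to 57%.

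**4. Week 8 named as primary.** The 2-df baseline-adjusted test has λ = 132 × (0.5² × 0.2222)/0.75 = 9.78 on 2 and 128 df. Power is 80% in all three rows of the last table.

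**5. Where the gain shrinks.** At δ = 0.25 each λ in step 3 is a quarter as large. Power goes from 16% to 21%, 20% to 29% and 20% to 22%. At ρ = 0.8 and δ = 0.5, variance 0.36 and covariance 0.16 give λ of 18.3 against 20.4 (steady), 24.4 against 28.2 (full by week 4) and 24.4 against 25.4 (week 8 only). Power is 0.943 against 0.965, 0.986 against 0.995 and 0.986 against 0.989.

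**The case against.** The protocol claims f = 0.125 and its N delivers f = 0.125. A reader might infer from the conversion that the trial is far less sensitive than it claims. The documents do not support that: they state no SD and no FMA difference that the trial then misses. The correlation of 0.5 is also back-solved from 132 and shows what was entered, not how FMA will behave. At ρ = 0.8 the planned test would detect 0.35 to 0.47 SD with 80% power, and at 0.9, 0.25 to 0.33 SD. This stands. The error is in the label and the missing translation.

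A reader might also infer that baseline adjustment recovers the lost power at no cost, most visibly through a single week-8 comparison. That does not hold either. Sections 4.0 to 6.0 ask about differences during the 8 weeks. Section 9.1.5 makes week 4 the end of a distinct phase, garment plus occupational therapy. Moving to week 8 alone changes the question. The gain also depends on the pattern: with both arms effective at 0.5 SD, ρ = 0.8 and the effect full by week 4 or present only at week 8, the week-8 test has power 0.985 against 0.986 for the interaction. Setting one garment contrast against the omnibus interaction would be unlike for unlike.

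Finally, a mixed ANOVA is a valid randomised comparison, and an SAP that is not shown may already specify covariates and contrasts. That lowers the weight of the analysis point. It does not repair the sample-size text.

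**Conclusion.** The point holds in two parts. First, the effect that section 9.1.2.3 powers is misdescribed: on the only test found to give 132, f = 0.125 is a largest week-8 difference of about 0.56 to 0.75 SD for regular patterns, and as low as about 0.46 SD for irregular ones. By the usual reading of standardised differences this is medium to large. The conversion assumes only no baseline difference and a common SD; the 80% attached to it also assumes ρ = 0.5 and sphericity.

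Second, the planned ANOVA leaves some power unused. A joint baseline-adjusted test over weeks 4 and 8 was at least as powerful as the interaction in every case computed. The gain was 5 to 18 percentage points at 0.5 SD, ρ = 0.5 and both compression arms effective. It is modest at ρ of 0.8 or more and small for true differences near 0.25 SD. These figures assume 132 completers and equal correlation between visits. The point should be corrected, but it does not invalidate the design.

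**What to change.** In section 9.1.2.3, name the group-by-time interaction as the powered effect, if Figure 4 confirms it, and state the assumed correlation and sphericity. Replace the small-to-medium label with the detectable between-arm difference in SD for stated effect patterns, and in FMA points under a stated SD.

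In section 9.1.6, make the primary FMA analysis a linear mixed model of week-4 and week-8 FMA with baseline FMA as covariate. Test the arm difference jointly over both visits, then make the pairwise garment contrasts. If the sponsor prefers week 8 as the primary time point, the 2-df baseline-adjusted test is an alternative, and a difference seen only at week 4 then becomes secondary.

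The cost is some wording and one model specification, fixed before unblinding. No more patients or visits are needed. The stated detectable effect will look less favourable than it does now.

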### 9.1.3 Research Location

This study will be conducted within the rehabilitation departments of three hospitals affiliated with Shandong Second Medical University, Weifang City, Shandong Province, China. These hospitals are the Affiliated Hospital of Shandong Second Medical University, Weifang Municipal People's Hospital, and Weifang Hospital of Traditional Chinese Medicine. These hospitals have equal medical and rehabilitation facilities and expertise, including the occupational therapy services.

The Rehabilitation Department of Weifang Hospital of Traditional Chinese

Medicine was established in 1997, operates 50 beds, 10 rehabilitation doctors, 20 rehabilitation therapists, and opening sections of physiotherapy, occupational therapy, etc. Over the years, the staff of the whole department has made unremitting explorations on the diagnosis and treatment of cerebrovascular disease, post-surgery of brain tumor, cerebral palsy, etc., and especially accumulated rich experience in the treatment of limb disorders caused by neurological injuries.

The Rehabilitation Department of Affiliated Hospital of Weifang Medical College is one of the earliest departments to carry out rehabilitation treatment in Weifang City. It currently operates 35 beds and departments of occupational therapy and physiotherapy, etc. It has 12 rehabilitation physicians and 14 rehabilitation therapists. Rich in experience of neurological rehabilitation, the hospital is equipped with advanced rehabilitation equipment, capable to carry out the tasks of treating more than 100 patients.

The Department of Rehabilitation of Weifang People's Hospital is a key clinical specialist facility in Weifang City, which currently operates 36 beds and both departments of occupational therapy and physical therapy. The hospital has nine rehabilitation physicians and 15 rehabilitation therapists to carry out comprehensive rehabilitative and medical works, including neurological rehabilitation, spinal cord injury rehabilitation, and post-surgical orthopaedic rehabilitation. The hospital is equipped with a complete set of modern assessment and rehabilitation therapy equipment.

#### **9.1.4 Research Instruments**

##### **9.1.4.1 Pressure Garment**

The pressure garments used in this study will be made and supplied by Klarity, China, with a Lycra content of 45 % and a polyamide content of 55 %.

###### **9.1.4.1.1 Determination of Compression Pressure**

Determination of compression pressure will be done using the Reduction Factor method

(Macintyre & Ferguson 2013), which is generally expressed as a percentage of stress (n%) depending on the tension generated by the pressure garment used. Different parts of the body, people, and styles of pressure garment require different percentages of stress. A typical pressure garment takes a value of 10% to 20% (Syron-Jones & Macintyre 2022). Considering that stroke patients do not need as much pressure as burn patients to inhibit scarring, we decided to use 10% stress. To achieve the predetermined stress, the dimensions required for fabrication of the take-up should be smaller than the actual measurements, the relationship of which can be expressed by the following equation:

$$L = X / (1 + 10\%)$$

X: actual measured value; L: calculated value required to produce a certain stress (Pratt & West 1995).

#### **9.1.4.1.2 Single-Layered 10% Circumferential Reduction (S-10) Pressure Garment**

The overall design of the single-layer pressure garment is similar to that of the anti-scarring pressure garment for burn patients. It is divided into the following main steps:

1. Making the compression arm sleeve.
  - (a) Measuring
  - (b) Drawing paper pattern
  - (c) Cutting and sewing.
2. Fabrication of the compression glove:
  - (a) Measurement of the fingers in the extended position, with each finger extended and abducted, with a soft ruler and recording the values.
  - (b) Drawing of sample paper
  - (c) Drawing of paper pattern for thumb
  - (d) Cutting and sewing

Following these steps, the final finished single layer pressure garment is shown in Figure 5.

[figure not shown]

Figure 5. Single-layered 10% circumferential reduction (S-10) pressure garment

#### **9.1.4.1.3 Dorsal Double-Layered 10% Circumferential Reduction (DD-10) Pressure Garment**

The overall approach to the DD-10 pressure garment is the same as that for the S-10 pressure garment with the main difference being that the dorsal side is simply secured using two pieces of fabrics of the same size, and then sewn together as a whole. The treatment on the thumb is simplified accordingly by not hollowing it out and measuring it along with the thumb when making the paper pattern, as shown in the Figure 6.

[figure not shown]

Figure 6. Dorsal double-layered (DD-10) pressure garment

#### 9.1.4.1.4 Single-Layered No Circumferential Reduction (S-0) Pressure Garment

S-0 is pressure-free pressure garment designed to be used as a control/placebo for this study. S-0 involves mainly the same fabrication process as SS-10 except it takes the value of 0 in the ratio of reduction. Thus, participants the control group will not feel constricted/compressed while wearing this pressure garment, as shown in the Figure 7.

[figure not shown]

Figure 7 Single-layered no circumferential reduction (S-0) pressure garment

Considering that pressure garment need to be washed regularly to ensure cleanliness and hygiene, and to prevent the growth of bacteria, each participant in this study will

be provided with two sets of identical pressure garment for easy replacement and cleaning.

#### **9.1.4.2 Demographic Form (Participant) (Appendix A)**

The Demographic Form (Participant) is designed to collect personal, family, and medical information related to stroke patients. This form contains five sections. The first section includes personal information, including name, age, gender, and contact information. The second section focuses on medical information, including type of stroke and sequelae. The third section is on lifestyle and social background, including marital status, education level, occupation, smoking history, and drinking history. The fourth section is on family status, including numbers of family members and caregivers. Finally, the fifth section allows participants to provide any additional comments or information.

#### **9.1.4.3 Assessment Instruments**

The assessment instruments include Fugl-Mayer Assessment of Upper Extremity as a primary outcome measure; Box and Block Test, Modified Ashworth Scale, Visual Analogue Scale, and Disabilities of Arm, Shoulder and Hand as secondary outcome measures; and Brunnstrom Recovery Stage and Saint Louis University Mental Status as screening measures.

##### **9.1.4.3.1 Fugl-Meyer Assessment of Upper Extremity (Appendix B) – Primary Outcome Measure**

The Fugl-Meyer Assessment (Kaufman et al.) of Upper Extremity is a classic tool used to assess the rehabilitation process of stroke patients. The assessment is known for its comprehensiveness and standardization and is designed to provide insight into the patient's motor function and level of life activities (Deakin et al. 2003). It has two main domains, the upper extremity and the lower extremity for systematically measure the patient's motor abilities. The upper extremity domain includes elements such as range

of motion of the shoulder, elbow, wrist and fingers, as well as grip strength and hand coordination. The lower extremity domain, on the other hand, focuses on hip, knee, and ankle mobility, as well as lower extremity muscle coordination and the patient's balance (Deakin et al. 2003). Aligning with the objectives of this study, only the upper extremity domain will be used.

The Fugl-Meyer assessment had high reliability with Interclass Correlation Coefficient (ICC) = 0.79 (Carmona et al. 2023) and excellent validity with  $r = 0.74-0.93$  ( $P < 0.0001$ ) (Jill See et al. 2013). The Chinese version had good reliability with ICC = 0.988 on test-retest and ICC = 0.959 on inter-rater (Kou et al. 2013). Its validity was highly correlated with Action Arm Research Test (ARAT) at 2 weeks ( $r = 0.91$ ) and at 8 weeks post-stroke ( $r = 0.94$ ),  $P < 0.01$  (Gladstone DJ et al. 2002).

#### **9.1.4.3.2 Visual Analogue Scale (Appendix C) – Secondary Outcome Measure**

The Visual Analogue Scale (Venckūnas et al.) is a scaling tool for subjective measures, often used to assess how an individual feels or sensed in a particular dimension (Shafshak & Elnemr 2021). It is a continuous scale that allows the person being assessed to indicate the degree of their subjective feelings by choosing a point between two extremes (Faiz 2014). The VAS is often used for pain assessment, assessment of emotional states, and other measures of subjective feelings. Typically, the two endpoints of the VAS are represented by extreme descriptions or emoticons. For example, in a pain assessment, one end of the scale might be "no pain" and the other end "worst pain" (Dourado et al. 2021). The person being assessed is asked to choose a point between the two endpoints that reflects their subjective feelings on that dimension. This can be done by drawing a vertical line, placing a marker, or other means (Reich et al. 2012).

The English version of the VAS had good reliability and validity, ICC = 0.97 (Bijur et al. 2001). It was strongly correlated with Numeric Rating Scale (NRS) with  $r = 0.92$  ( $P < 0.001$ ) (Shafshak & Elnemr 2021). The Chinese version also had good reliability, ICC = 0.73 and in terms of validity, it was strongly correlated with NRS,

Verbal Descriptor Scale (VDS), and the Faces Pain Scale Revised (FPS-R) ( $r = 0.71-0.99$ ) (Li et al. 2007).

#### **9.1.4.3.3 Disabilities of Arm, Shoulder and Hand Outcome Measure (Appendix D)**

##### **– Secondary Outcome Measure**

The Disabilities of Arm, Shoulder and Hand (DASH) Outcome Measure is a widely used measurement tool for assessing upper extremity function. It provides a comprehensive and reliable way to assess the outcome of patients with dysfunctions of the arm, shoulder and hand, particularly in conditions such as trauma, surgery or chronic pathology (Hudak et al. 1996). The DASH measure consists of a 30-items that covers a wide range of functional problems that patients face in their daily lives. These questions cover a wide range of aspects, including life activities, symptoms, social roles and psychological aspects (Beaton, Katz, et al. 2001). Patients are asked to answer the questions based on their own experience, and a score is used to reflect the degree of dysfunction in different areas, with a score of 0 indicating no dysfunction and a score of 100 indicating the most severe dysfunction (Beaton, Davis, et al. 2001).

The English version of DASH had high reliability, ICC = 0.84-0.97 (Sigirtmac & Oksuz 2021). It is strongly correlated with NDII Score ( $r = -0.86$ ) (Goldstein et al. 2015). The Simplified Chinese version of the DASH, translated by [name], available via DASH official website will be used in this study.

Permission to use the simplified Chinese version has been obtained from the author of this translated version, China-Japan Union Hospital of Jilin University (Appendix D2).

#### **9.1.4.3.4 Box and Block Test (Appendix E)– Secondary Outcome Measure**

The Box and Block Test (BBT) is a quantitative tool commonly used to assess upper extremity sensorimotor function. The test is designed to measure extremity coordination, dexterity, speed of movement, fine motor skills. It is a simple but effective test that is widely used in the field of rehabilitation, clinical practice, and scientific research. BBT requires the patient to move a set of cubes from one side of a box

separated into two equal-sized compartments to the other side, with a divider to prevent the cubes from falling out (Oliveira et al. 2016). BBT is assessed based on the number of cubes the patient successfully transfers in 1 minute. Typically, the faster the patient and the greater the number of blocks transferred, the better the upper extremity dexterity is considered to be. This makes the BBT an easy and objective measure (Chanubol et al. 2012), as shown in Fig. 8.

The reliability of the English version of the BBT is also relatively high, with ICC= 0.92-0.97, correlated the arm function test ( $r = 0.59$ ) (Desrosiers et al. 1994). The reliability of the Chinese version using affected hand ICC= 0.975, using un-affected hand ICC= 0.982 (Li et al. 2020). The validity is also better (Li et al. 2020).

